### 1.1. Measurement of compliance

Each of the six domains of perioperative infection prevention include two or more related behaviors. The result of each domain is measured as a binary, where 1 = all behaviors in the domain were performed during the procedure, and 0 = at least one of the behaviors was not performed.

To capture overall compliance, we will construct a “high compliance” flag where:

1 = 5 or 6 domains were performed in the surgery

0 = 0 to 4 domains were performed in the surgery

We based this cut point between 4 and 5 on the global distribution of compliance scores. This cut point roughly splits the cases: about half were high compliance, half were not.

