## **Program Evidence**

Lifebox developed Clean Cut as a multimodal, adaptive, checklist-based improvement program following an extensive consultation with providers and practitioners from around the world who identified surgical infections as a major source of preventable surgical morbidity and mortality. The program was introduced in Ethiopia, initially in conjunction with the Surgical Society of Ethiopia and then through partnerships with the FMOH. Clean Cut was first evaluated at Jimma University Specialized Hospital in 2016, with the pilot work extending to five initial hospitals where we prospectively collected compliance data from 2213 operations (374 during baseline assessment and 1839 following implementation of process improvements) in 2202 patients with follow up in 2159 patients (98.0%). At baseline, perioperative teams only complied with an average of 2.9 of the six critical perioperative infection prevention standards; following process improvement changes, compliance rose to 4.5 ( $p < 0.001$ ). The relative risk of surgical infections following Clean Cut implementation was 0.65 (95% CI 0.43-0.99;  $p = 0.043$ ). Improved compliance with standards reduced the risk of postoperative infection by 46% (RR 0.54 for adherence score 3-6 vs 0-2; 95% CI 0.30-0.97;  $p = 0.038$ ).

Since then the program has been implemented in 11 hospitals and has benefitted an estimated 34,000 patients. In our preliminary, unpublished analyses of 8 hospitals with completed data, we have prospectively collected compliance data from 2905 operations, of which 1133 (39%) were CS or hysterectomy, with an average monthly volume of 27 obstetric operations per facility. Of the total, 2692 patients (92.7%) had outcomes follow-up, with 1075 (40%) being obstetric patients. After program implementation, significant improvements were seen in each of the IP areas: instrument decontamination, gown and drape integrity, surgical skin antisepsis, gauze counting, antibiotic administration, and use of the surgical safety checklist. At baseline, unadjusted SSI rate was 11.3% overall and 12.4% for the obstetric group; after Clean Cut implementation, the SSI rate fell to 6.2% overall and 6.6% in the obstetric group (a 47% decrease).

---

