**Figure 2: Monthly recruitment rates needed to detect selected outcome proportions**

[figure not shown]

**Analysis:** We will conduct pre/post analyses using the statistical approach recommended by Hemming with our planned assessment controlling for risk factors and other demographic and procedure variables listed below that are known to affect infection rates. We will compare patient demographics pre and post intervention as well to evaluate overall matching of patients in each part of the study. We will evaluate compliance individually and in an all-or-none manner as previously described in our Clean Cut pilot work. We will undertake a planned subanalysis of patients observed early during baseline (first two months) and compare them to patients undergoing surgery during the

final stage of the study (last two months) after implementation of the program has had time to take effect to assess primary and secondary outcomes.

As we are interested not only in the primary outcome of surgical infection but also in process improvements and the implementation strategies and support that can lead to effective compliance with best practices, we will not conduct any interim analyses. The purpose of an interim analysis is to assess the study for benefit, futility or harm. We believe that neither benefit nor futility would be readily observable at an interim analysis given the implementation strategy and approach; furthermore, even if we were able to assess benefit or futility we would want to continue the trial to fully study the mechanisms of implementation. Regarding an assessment of harm, if such an outcome were noted we believe this would most likely be due to detection bias with improving ability to capture complications as the study progressed, and we would want to let the study play out to mitigate this detection bias over time.

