### 1.2. Multiple comparisons

This analysis includes 6 aims, which collectively involve fitting 12 models (Table 7). Each model has a single predictor of interest, which is the intervention variable in all models except in aim 6, where the predictor of interest is the flag for high-compliance surgeries. We will evaluate each p value against an alpha of 0.05 and will not adjust for multiplicity.

Table 7: Number of planned models across all aims

|            |       |                                                | N models |
|------------|-------|------------------------------------------------|----------|
| Primary    | Aim 1 | Infection reduction in CS                      | 1        |
| Secondary  | Aim 2 | 6 compliance domains, 1 overall score          | 7        |
|            | Aim 3 | Reduced maternal postoperative mortality       | 1        |
|            | Aim 4 | Reduced neonatal mortality                     | 1        |
| Additional | Aim 5 | SSI, maternal mortality, or neonatal mortality | 1        |
|            | Aim 6 | Compliance, surgical infection                 | 1        |

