#### 8.7 Aim 6: Relate compliance to SSIs

Our overall theory of change is that the intervention will cause higher compliance with proven infection prevention behaviors, which will in turn cause a reduction in SSIs. In other words, if the intervention proves effective, then we would expect it to work through the mechanism of raising compliance scores. We will test this theory by swapping out the intervention indicator variable for the indicator of a high-compliance operation.

Then, using the CS population with follow-up, we will build the same model as our primary analysis except to drop intervention status and replace it with the high compliance binary variable. This will become the predictor of interest for this aim only.

We will interpret this OR in light of the results on aim 1. That is, if the intervention is effective, then we expect that the “intervention phase” binary variable and the “high compliance operation” binary variable will capture highly overlapping cases. In fact, the more successful the intervention, the more strongly these two variables will be correlated. If the intervention succeeds in aim 1 then we will expect the OR for high compliance in this model to be of the same direction ( $<1$ ) and roughly comparable in significance.

If the intervention does not succeed in aim 1, then this model will function like an assay sensitivity test. The infection reduction activities in Clean Cut are extraordinarily well established in the clinical and public health literature. If we find that higher compliance operations are *not* associated with SSI rates, that will cast doubt on all the trial results and pose larger questions about measurement, data quality, and our implementation strategy in this trial.

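### Aim 6 tests compliance against SSI only through a data-derived 5-6 versus 0-4 flag, which can miss an effect at the low end of the score, yet a null after a negative Aim 1 would be read as doubt on the whole trial

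*Combined protocol and SAP*

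**What the plan says.** The SAP section on measurement of compliance (under section 7) scores each of six domains as met or not met, then builds one overall flag: "1 = 5 or 6 domains were performed in the surgery" and "0 = 0 to 4 domains were performed in the surgery". It gives the basis for the threshold, "We based this cut point between 4 and 5 on the global distribution of compliance scores", and adds: "This cut point roughly splits the cases: about half were high compliance, half were not". No clinical or pilot rationale is offered.

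The pilot result in the protocol (Program Evidence) used a different split: "RR 0.54 for adherence score 3-6 vs 0-2; 95% CI 0.30-0.97". The protocol's Analysis paragraph said: "We will evaluate compliance individually and in an all-or-none manner as previously described in our Clean Cut pilot work".

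The flag has two uses. In Aim 2 (SAP 8.3) it is the outcome of the seventh model, after one model per domain; Table 7 lists these as "6 compliance domains, 1 overall score". In Aim 6 (SAP 8.7) it replaces the intervention term in the primary model and is the only predictor of interest. If Aim 1 is negative, the SAP gives Aim 6 the role of an assay-sensitivity test, and says that finding no association is something "that will cast doubt on all the trial results and pose larger questions about measurement, data quality" and the implementation strategy. Section 9 plans no other coding of compliance.

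**The concern.** An assay-sensitivity reading is sound only if the test would probably have picked up a real effect. The only evidence in the documents on where the score relates to infection is the pilot contrast of 0-2 with 3-6. The SAP flag keeps 5-6 apart and puts 3-4 together with 0-2. If the gain in infection risk comes from leaving the 0-2 range, the 0-4 group becomes a mixture in which the high-risk cases are diluted by low-risk ones, and the flag's odds ratio moves towards 1.

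What is at stake is an interpretation, not the primary result. After a negative Aim 1, a null flag would lead the authors to question measurement and data quality across the trial, when the cut point alone could have produced the null. The SAP states no power for Aim 6 and gives no score distribution from which a reader could judge this.

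**Working it through.** **Pilot figure.** RR 0.54 is a 46% reduction, as stated. From the interval, SE(log RR) = (ln 0.97 − ln 0.30)/3.92 = 0.299, so z = ln 0.54/0.299 = −2.06 and p ≈ 0.040. This agrees with the reported 0.038 within rounding. The SAP's half-and-half split cannot be reproduced, because the score distribution is not given.

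**Inputs.**
- RR 0.54 for 3-6 versus 0-2 (protocol, Program Evidence).
- Half of cases at 5-6 (SAP, measurement of compliance).
- Two-sided 5% test. The SAP gives 0.05; two-sided is assumed.
- N = 4,500 audited caesarean cases (assumed). SAP Table 3 gives 5,525 for all audited operations, although its arm totals 2,764 + 2,828 add to 5,592. The caesarean-only number is not stated.
- Overall SSI 6% (assumed low case) and 9%. SAP 4.2 expects 9% to 12% in the control condition.
- L, the share of all cases scoring 0-2: 5% to 20% (assumed).

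**Dilution if the whole effect sits between 2 and 3 domains.** Let the risk be r at 0-2 and 0.54r at 3-6, with overall risk S.
- r = S / [L + 0.54(1 − L)]
- Risk at 5-6 = 0.54r
- Risk at 0-4 = [L·r + (0.5 − L)·0.54r] / 0.5
- Flag RR = 0.54 / {[L + 0.54(0.5 − L)] / 0.5}
- Power = Φ(|difference|/SE − 1.96), with unpooled SE, N/2 per group, and no clustering, month or covariate terms

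**Example, L = 10% and S = 6%.** r = 0.06/0.586 = 0.1024. Risk at 5-6 is 0.0553. Risk at 0-4 is (0.01024 + 0.4 × 0.0553)/0.5 = 0.0647. RR = 0.85. SE = √(0.0647 × 0.9353/2250 + 0.0553 × 0.9447/2250) = 0.0071. The difference of 0.0094 gives a ratio of about 1.33, so power = Φ(−0.63) ≈ 26%.

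| Share at 0-2 | Flag RR | Flag power, SSI 6% | Flag power, SSI 9% | Pilot-cut power, SSI 6% |
|---|---|---|---|---|
| 5% | 0.92 | 10% | 14% | 65% |
| 10% | 0.85 | 26% | 38% | 89% |
| 15% | 0.80 | 48% | 67% | 96% |
| 20% | 0.75 | 69% | 87% | 99% |

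Under this shape, 80% power with N = 4,500 needs about 18% of all cases at 0-2 when SSI is 9%, and about 15% when it is 12%. With N = 5,525 the shares are about 16% and 13%.

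**Other shapes.** If the same RR of 0.54 instead sits between 4 and 5 domains (N = 4,500, SSI 6%), r = 0.06/(0.5 + 0.5 × 0.54) = 0.0779 at 0-4 and 0.0421 at 5-6. Flag power is then over 99%, while the pilot cut has only about 18-64% for 5-20% at 0-2. With a graded effect per domain, scaled to reproduce 0.54 for 3-6 versus 0-2, the flag RR is about 0.55-0.64 and power is 96% or more in every scenario run at N = 5,525 with SSI 5-12%.

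**The 0-6 score as a trend term** (N = 4,500, SSI 6-9%, assumed distributions with 4-23% at 0-2). With a step between 2 and 3 it has 26-37% power against 8-10% for the flag when few cases score 0-2, and 93-99% against 51-69% when about 15% do. If the true step is between 4 and 5 it loses modestly, for example 35% against 47% for an RR of 0.8.

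**The case against.** The strongest reply is that the calculation assumes its conclusion: put all the effect between 2 and 3 domains, and a cut there wins. The pilot reports one dichotomy with a wide interval. It shows neither a threshold at that point nor a flat risk above it. Under a graded effect, or a step at the SAP's cut, the flag does well. The share scoring 0-2 is also unknown; illustrative overdispersed scores put it at up to about 28% of all cases (57% of the 0-4 half), where the flag's power at 9% SSI exceeds 99%. This stands, and it makes the risk conditional. It does not rescue the assay-sensitivity reading, because the SAP has not shown that the favourable case applies.

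A reader might also infer several stronger points that the documents do not support.
- **The flag merges the pilot's two groups.** It does not. It pools 0-2 with 3-4 and keeps 5-6 separate.
- **The cut was tuned to the infection result or inflates type I error.** The stated basis is the distribution of compliance scores. Nothing says that SSI data were consulted.
- **The SAP dropped a promised six-of-six outcome.** The protocol's all-or-none wording refers to pilot work not reproduced here. It could equally describe the within-domain rule, which the SAP does apply.
- **Aim 2 cannot see improvement below five domains.** The six single-domain models would register most of it. Only the summary model is blind to it.
- **Aim 6 decides the trial.** Table 5 lists it as an additional aim that was not pre-specified, and the assay reading applies only if Aim 1 is negative.

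**Conclusion.** The concern holds in conditional form. Aim 6 rests on one flag, cut near the observed middle of the pooled scores, and its departure from the pilot's contrast is unexplained. If the effect lies mainly at the low end and 5-20% of cases score 0-2, a pilot-sized effect appears as an RR of about 0.92 to 0.75. The flag would then detect it with about 10-69% power at 6% SSI, or 14-87% at 9%. These figures assume 4,500 caesarean cases and half of cases at 5-6. They ignore clustering, month and covariates, so they are probably optimistic.

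It does not follow that Aim 6 will fail. With a graded effect or a step between 4 and 5 domains the flag has good power, and the documents give neither the score distribution nor the shape. What they do not support is reading a null on this flag alone as evidence against the trial's data. The primary result is unaffected.

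**What to change.** In Aim 6, add two codings to the flag: the number of domains met (0-6) as a per-domain trend, and the categories 0-2, 3-4 and 5-6. Report the score distribution, overall and by condition. State that the assay-sensitivity reading will be drawn from these codings together with the flag, never from the flag alone. Keep the flag, label it as derived from the observed scores, and give the reason for leaving the pilot's split.

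In Aim 2, report the mean 0-6 score beside the flag as a supplement. Replacing the flag there is optional, because the six domain models already capture most changes.

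The cost is SAP wording and one or two extra models on data already collected. The trend term loses a little power if the true step is between 4 and 5 domains, which is one reason to keep the flag alongside it.

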### 1.2. Multiple comparisons

This analysis includes 6 aims, which collectively involve fitting 12 models (Table 7). Each model has a single predictor of interest, which is the intervention variable in all models except in aim 6, where the predictor of interest is the flag for high-compliance surgeries. We will evaluate each p value against an alpha of 0.05 and will not adjust for multiplicity.

Table 7: Number of planned models across all aims

|            |       |                                                | N models |
|------------|-------|------------------------------------------------|----------|
| Primary    | Aim 1 | Infection reduction in CS                      | 1        |
| Secondary  | Aim 2 | 6 compliance domains, 1 overall score          | 7        |
|            | Aim 3 | Reduced maternal postoperative mortality       | 1        |
|            | Aim 4 | Reduced neonatal mortality                     | 1        |
| Additional | Aim 5 | SSI, maternal mortality, or neonatal mortality | 1        |
|            | Aim 6 | Compliance, surgical infection                 | 1        |

## 8 Statistical analyses

### 8.1 Demographic and clinical characteristics

We will describe the demographic and clinical characteristics of each of our study populations and compare the control and intervention groups. We will include characteristics such as age, presence of diabetes or hypertension, American Society of Anesthesiologists (ASA) classification, wound class, case urgency, the presence of ruptured membranes, and indication for caesarean section.

To avoid the risks of false discovery, we will not perform statistical tests or present p-values comparing across arms in these descriptive tables.

### 8.2 Aim 1: Infection reduction in CS

We will build our primary model using the CS population with follow-up, and the outcome will be an SSI within 30 days of the procedure. If the estimated OR of having an SSI under the intervention is less than 1 and statistically significant, then we will conclude a positive effect of the intervention on SSI rates.

### 8.3 Aim 2: Improved compliance with infection prevention practices

Using the total intraoperative population, we will report percentages of compliance for each of the six key areas of infection prevention in the control and intervention groups. Then, we will construct six models using each binary in turn as the dependent variable, and dropping the vector of demographic variables, which are not likely to be causally related to compliance. If the estimated OR of a behavior being performed under the intervention is greater than 1 and statistically significant, then we will conclude a positive effect of the intervention on that behavior. Finally, we will fit a last model using “high compliance” (defined as a compliance score of >4) as the outcome.

### 8.4 Aim 3: Reduced maternal postoperative mortality

We will build this model using the CS population with follow-up, and the outcome will be maternal mortality within 30 days of procedure. We expect maternal deaths to be rare and note that the study is not powered to detect a change in such a rare event. Otherwise, the model features and interpretation will be the same as the primary model.

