**Secondary:**

2. *Surgical infections following obstetric and gynecologic operations*: Number of patients undergoing obstetric and gynecologic operations diagnosed with postoperative infection in hospital or up to 30 days post surgery; measured by change pre and post intervention
3. *Compliance with infection prevention practices*: Number of patients undergoing obstetric and gynecologic surgery receiving each of the six perioperative infection prevention and control practices defined by the Clean Cut program; measured by change pre and post intervention
4. *Reoperation following obstetric and gynecologic surgery*: Number of patients requiring reoperation or return to the operating theatre prior to discharge following obstetric and gynecologic surgery; measured by change pre- and post-intervention

5. *Length of Stay*: Mean and median length of stay, in days, following obstetric and gynecologic surgery; measured by change pre- and post-intervention
6. *Postoperative maternal mortality*: Number of mothers who die in hospital or up to 30 days following CS; measured by change pre- and post-intervention
7. *Postoperative mortality*: Number of women who die in hospital or up to 30 days following obstetric and gynecologic surgery; measured by change pre- and post-intervention
8. *Neonatal mortality*: Number of newborn/fetal deaths prior to discharge of mother following cesarean delivery; measured by change pre- and post-intervention

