## Clean Cut Outpatient Data Collection Form

### 30-day postoperative follow-up: To be conducted 30 days after SURGERY

Hospital: \_\_\_\_\_ Data Collector Name: \_\_\_\_\_

|                                                                          |                                                                                                   |
|--------------------------------------------------------------------------|---------------------------------------------------------------------------------------------------|
| Patient Name                                                             |                                                                                                   |
| Card/ Medical Record No.                                                 |                                                                                                   |
| Date of Surgery
(International Calendar)                              |                     
(Month, dd, yyyy)                                                  |
| Date of Discharge
(International Calendar)                            |                     
(Month, dd, yyyy)                                                  |
| Date of Phone call
(International Calendar)                           |                     
(Month, dd, yyyy)                                                  |
| Patient Status                                                           | Alive    -or-    Dead                                                                             |
| Neonate Status (if post-Cesarean)                                        | Alive    -or-    Dead                                                                             |
| Did your wound open up?                                                  | Yes    -or-    No                                                                                 |
| Is there drainage from the wound?                                        | Yes    -or-    No                                                                                 |
| → If yes, What kind of drainage?                                         | Serous   Pus   Bloody   Feculent   Other: _____                                                   |
| Have you visited a healthcare provider since discharge?                  | Yes    -or-    No                                                                                 |

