## Outpatient (Phone) Data Collection Tool Guide

| Outpatient (Phone) Follow Up Form      |                                                     |                                                                                                                                                                                                                                                                                                                                                                                                                                                                                                         |
|----------------------------------------|-----------------------------------------------------|---------------------------------------------------------------------------------------------------------------------------------------------------------------------------------------------------------------------------------------------------------------------------------------------------------------------------------------------------------------------------------------------------------------------------------------------------------------------------------------------------------|
| Patient Status                         | Alive / Dead                                        | Is the patient confirmed alive or dead at the phone call?                                                                                                                                                                                                                                                                                                                                                                                                                                               |
| Neonate Status                         | Alive / Dead                                        | If case is Caesarean section, is the neonate confirmed alive or dead at the phone call?                                                                                                                                                                                                                                                                                                                                                                                                                 |

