## 4. Audit of 30-day follow-up data

### 4.1. Background

In May 2022 the study team became concerned that SSI rates at 30-day phone follow-up were too low relative to lived experiences of Ethiopian clinicians and published data on SSI rates in Ethiopia following caesarean section, calling into question the quality of the follow-up data. We were concerned the data collectors were missing a significant number of SSI on 30-day follow-up. Although we had robust in-hospital SSI data, most SSIs occur after hospital discharge, and total (inpatient and 30-day) SSI rate is the primary outcome of this study. For these reasons, we decided to audit outcomes on the entire sample using staff with more clinical and research training. Beginning in August 2022, we recruited and trained general practitioners on the 30-day follow-up data collection tool, and between September 2022 and March 2023, these auditors called all patients and re-collected 30-day follow-up data retrospectively. The original set of data collectors continued to collect follow-up data as well.

In this SAP, we refer to the initial group of workers whose data was called into question as the “data collectors,” and the more trained workers who replicated the follow-up calls as the “auditors.”

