### *CS population with follow-up*

All CS patients enrolled in the study who have complete 30-day follow-up data collected by the auditors.

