### 8.5 Aim 4: Reduced neonatal mortality

We will build this model using the CS population with follow-up, and the outcome will be neonatal mortality within 30 days of procedure. While our study protocol states we would capture this data prior to the mother’s discharge, we observed a significant proportion of neonatal deaths after the mother was discharged from the hospital, likely reflecting a longer

clinical course for an unwell neonate than a healthy mother. We agreed to include neonatal mortality collected up through 30 day phone follow-up. We expect neonatal deaths to be rare and note that the study may not have the power to detect a change. Otherwise, the model features and interpretation will be the same as the primary model.

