#### 8.6 Aim 5: Composite outcome

We will build this model using the CS population with follow-up, and the outcome will be a composite of SSI, maternal mortality, or neonatal mortality within 30 days. Otherwise, the model features and interpretation will be the same as the primary model. Since SSIs are more common than maternal or neonatal deaths, we expect the results of this model may be similar to the primary model.

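### The mortality aims and the composite exclude deaths already on record when the auditor did not complete a call, and the auditors' form cannot date post-discharge deaths to 30 days

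*Combined protocol and SAP*

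**What the plan says.** - **Population.** SAP 8.4 (Aim 3): "We will build this model using the CS population with follow-up, and the outcome will be maternal mortality within 30 days of procedure". SAP 8.5 (Aim 4) and 8.6 (Aim 5) use the same population. SAP 6 defines it as "All CS patients enrolled in the study who have complete 30-day follow-up data collected by the auditors".
- **Outcomes.** Aim 4 moves the protocol's neonatal endpoint, "Number of newborn/fetal deaths prior to discharge of mother following cesarean delivery", to a 30-day window: "We agreed to include neonatal mortality collected up through 30 day phone follow-up". For Aim 5, "the outcome will be a composite of SSI, maternal mortality, or neonatal mortality within 30 days".
- **Source.** SAP 4.1 says that, between September 2022 and March 2023, "these auditors called all patients and re-collected 30-day follow-up data retrospectively". SAP 4.3 adopts the auditors' data for every follow-up measure. SAP Table 1 still lists in-hospital records as a source for maternal and neonatal death.
- **Instruments.** The phone form is headed "30-day postoperative follow-up: To be conducted 30 days after SURGERY". Its guide defines maternal status as "Is the patient confirmed alive or dead at the phone call", with a matching item for the neonate and no date of death. The inpatient form has one dated row per day, with columns for maternal and neonatal death.
- **Model.** Aims 3 to 5 keep the primary model: 18 categorical months, intervention, eight controls and a cohort random effect.

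**The concern.** Whether a patient enters the mortality analysis depends on a completed retrospective call, often many months after surgery. A mother or baby whose death is already documented is left out if that call failed. A bereaved or dissolved household may be harder to reach, and the SAP does not say whether a woman who died can have complete follow-up. Inclusion may therefore depend on the outcome.

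The phone form suits a call at day 30, when status at the call is day-30 status. Used months later, it records death by the call, which is not the stated endpoint.

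The SAP's evidence against the data collectors (3.2, 4.1, 4.2) concerns implausibly low infection rates and does not examine vital status. The planned checks on fieldwork staff, loss to follow-up and recall all concern infection. The argument that recall bias is conservative concerns forgotten infections and does not carry over to deaths.

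**Working it through.** **1. Coverage (SAP Table 4, all enrolees).**
- Auditors: control 2,764/5,715 = 48.4%; intervention 2,828/4,951 = 57.1%; together 5,592/10,666 = 52.4%. These reproduce the SAP's 48%, 57% and 52%. (Table 3 prints a total of 5,525, which gives 51.8%; its two conditions sum to 5,592.)
- Data collectors: 5,561/5,715 = 97.3%; 4,592/4,951 = 92.7%; together 10,153/10,666 = 95.2%.
- Difference: 10,153 − 5,592 = 4,561 patients. Standard-error ratio, clustering ignored: √(10,153/5,592) = 1.35.

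**2. Deaths at stake (illustration).** Apply the protocol's national rates of 30 per 1,000 neonatal and 401 per 100,000 maternal. The counts include non-caesarean patients, so at these rates the results are upper bounds.
- Neonatal: 5,592 × 0.030 = 168, against 10,153 × 0.030 = 305.
- Maternal: 5,592 × 0.00401 = 22, against 10,153 × 0.00401 = 41.

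**3. Timing of the auditor calls.** From the end of the control period (SAP Table 3) to the earliest call on 1 September 2022 is 247, 184, 115 and 52 days for cohorts 1 to 4. So 111 + 422 + 600 + 783 = 1,916 of 2,764 audited control patients (69%) were called at least 52 days after surgery. For an August 2021 operation the stated dates allow 12 to just under 20 months; the SAP says up to a year.

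**4. Does the longer control window bias the intervention estimate?** Assume no true effect, 3.0% neonatal death by day 30, a further d = 0.5%, 1.0% or 2.0% spread evenly over months 1 to 12, auditor counts spread evenly over each cohort's months, and calls uniform from September 2022 to March 2023 on one schedule for all cohorts.
- Crude odds ratio of status at the call: about 0.91, 0.84 and 0.73 (up to 0.92, 0.85 and 0.75, depending on how the run-in weeks are handled).
- With the planned month terms: recorded risk for surgery in month m is 0.03 + d × g(m), where g(m) is the share of months 1 to 12 elapsed by the call. It is the same in both conditions, so the within-month odds ratio is 1. Fitting it gives 1.000 in all three cases, with or without cohort terms.
- With a linear time term instead: 0.99 to 0.95.

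**5. Selective reach.** If families with a death are reached at f_C (control) and f_I (intervention) times the rate of other families, the null odds ratio is f_I/f_C. Assumed values: 0.75/0.5 = 1.5; 1/0.5 = 2.0; 1/0.75 = 1.33. Month terms remove this only if relative reach depends on month of surgery alone. The documents give no reach by survival status.

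**6. Size of the Aim 3 model.** 17 month contrasts + 1 intervention term + at least 8 control coefficients = 26. 22.4/26 = 0.86 deaths per coefficient. With deaths spread evenly, months without a death: 18 × exp(−22.4/18) = 5.2.

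**The case against.** A reader might infer that the longer control window biases mortality in favour of the intervention. The documents do not support that for the planned model. With one call schedule the month terms remove the effect, and no passage says that cohorts were called on different schedules. Selective reach could push the other way.

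Other fair points:
- A reader might infer near-complete ward data. Ward completeness is never quantified; the 95% is the data collectors' phone coverage, which falls to 87% in intervention cohorts 4 and 5.
- Because Table 1 keeps in-hospital records as a source, status at the call matters only for post-discharge deaths. That the auditors recorded no timing is inferred from the form.
- The SAP labels the data collectors' phone data poor and made a considered choice against them. Calls that missed infections are not thereby shown to be sound on vital status. This stands, and calls for a concordance check.
- SAP 8.5 gives a disclosed reason for the 30-day neonatal window: many deaths followed the mother's discharge. Going back to pre-discharge death as the main endpoint would discard them.
- Sparse data are a problem for Aim 3 only. Aim 4 could have about 168 deaths, and infection dominates Aim 5. The SAP already concedes low power for Aims 3 and 4.

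None of this explains why a death on a dated ward form should be dropped because a later call failed.

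**Conclusion.** The point holds as a problem of excluded outcomes, precision and endpoint definition. Aims 3 to 5 rest on about 52% of enrolees when day-30 vital status is held for about 95%. At national rates that is roughly 168 rather than 305 neonatal deaths and 22 rather than 41 maternal deaths, with standard errors about 1.35 times larger. These figures assume that all-enrolee coverage and national rates apply to the caesarean patients. Post-discharge deaths first found by an auditor cannot be placed within 30 days from the form as published.

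The net direction of bias is unknown. It depends on whether cohorts shared a call schedule and on how survival affected reach, and the documents give neither. Two secondary aims and one added composite are affected; the primary analysis is not.

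**What to change.** - **Aims 3 and 4.** Analyse all enrolled caesarean patients. Count a maternal or neonatal death within 30 days if it is on the ward form or in the data collectors' day-30 call. Use auditor data only where these are missing: alive at a later call settles day-30 status, while a death counts only if it can be dated within 30 days. Report how many remain unknown.
- **Aim 4.** Keep the SAP's 30-day window; report the protocol's pre-discharge definition as supplementary.
- **Checks.** Report vital-status agreement between collectors and auditors in women reached by both. Keep the auditor-only analysis as a sensitivity run with the categorical month terms.
- **Aim 5.** Leave the infection component with the auditors. As a sensitivity analysis, count any recorded ward or day-30 death as an event even when the auditor did not reach the woman. Do this in the imputed data set already planned for loss to follow-up, so that unreached survivors enter the denominator too; adding only the deaths would select on the outcome.
- **Aim 3 model only.** Drop the eight controls and use a penalised fit.

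Cost: SAP wording and re-derivation of three variables from data already held. Downside: vital status would rest partly on collectors whose phone data the SAP distrusts for infection; the agreement table and the auditor-only run show how much that matters.
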